#### SCR group

For autogenous fascia latas, the size of the rotator cuff tear and superior capsule were evaluated in both the anteroposterior and mediolateral directions at 45 shoulder abduction by using a measuring probe. The width of the autogenous fascia latas patch was measured from the anterior to the posterior edge of the rotator cuff tendon lesion. The length of the autogenous fascia latas patch was based on the distance from the lateral edge of the rotator cuff footprint and the medial side of the superior glenoid. Autogenous fascia latas was fold for double layers and the thickness was guaranteed to be 6–8 mm. Two threaded anchors were inserted 5–6 mm above the medial side of the superior glenoid according to the surgical condition. Two anchors were inserted behind the midline of the scapula at the 10 to 11 o’clock and 11 to 12 o’clock positions. For the outer anchors, a double-row repair technique was performed on the footprint.

### Criteria for discontinuing or modifying allocated interventions {11b}

Intraoperative examination found that the rotator cuff of the subject was “repairable” (if it was determined that the ruptured rotator cuff could be directly repaired during the operation, conventional repair of the ruptured rotator cuff, namely direct repair, would be performed).Deciding to withdraw from the trial at any time and for any reason.Loss to follow-up.

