### Eligibility criteria {10}

#### Inclusion criteria

Age 50–85 years old.Massive rotator cuff tear identified by preoperative MRI imaging technology (sagittal anterior and posterior tear length ≥ 5 cm or involving two or more rotator cuff tendon tears).The intraoperative evidence was IPMRCT (standard for irreparable rotator cuff injury: after full release, tissue forceps were used to test the tension of the broken rotator cuff stump, and it was found that the rotator cuff stump could not effectively cover the footprint under moderate pulling tension).Preoperative imaging examination Hamada classification within type 3.Agree to undergo arthroscopic STR or SCR operation.

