### Who will take informed consent? {26a}

Patients with IPMRCT who met the inclusion will choose whether to join the clinical trial in the outpatient department. [name] will inform the patients with IPMRCT that they have met the inclusion criteria for the clinical trial. After confirming the patient’s eligibility for inclusion and completing a baseline-level assessment, the main investigator will give a detailed presentation of the study protocol and potential risks and answer all the questions raised by patients and their families. Each participant who meets all inclusion criteria and does not meet any exclusion criteria will sign an informed consent form. Upon enrolment, participants will be coded with a unique number.

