### Strategies to improve adherence to interventions {11c}

All surgical procedures were performed by the same senior doctor and the same 5-person group.

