## Assignment of interventions: allocation

### Sequence generation {16a}

Randomization will be performed using a computerized randomization procedure in https://castoredc.com. The enrolled patients were randomized in a 1:1 ratio into two treatment groups (the STR group and the SCR group). Patients will be randomized in a 1:1 ratio using variable block sizes of two, four and eight patients, stratified for two treatment groups (the STR group and the SCR group) to avoid imbalances between groups. The order of the block sizes is unknown to the researchers.

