### Concealment mechanism {16b}

The random assignment form is usually triplicated. Copies can be enclosed in an opaque envelope, with one copy provided to the patient, one copy to the researcher and one copy to the evaluator. The patient and researchers unseal it before surgery. The allocation scheme is not disclosed to the evaluators collecting outcome data throughout the study. The statistical analysts will also not know whether participants are in the STR or SCR group until the statistical analysis is completed.

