### Procedure for unblinding if needed {17b}

Because a surgical procedure is involved, the surgeons including the principal investigator were unblinded to the trial, and the evaluators collecting outcome data did not join the operation and were blinded throughout the study. When there is serious adverse event reporting and harms or the trial is finished, it will be unblinded.

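### Allocation is opened before surgery, but irreparability, an inclusion criterion, is judged during surgery by a surgeon who knows the arm

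*Protocol article*

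**What the plan says.** Four statements in the protocol article fix the order of events.

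- **Inclusion criteria:** the tear must be shown irreparable in theatre ("The intraoperative evidence was IPMRCT"). The standard is that, after full release and traction with forceps, "the rotator cuff stump could not effectively cover the footprint under moderate pulling tension".
- **Concealment mechanism {16b}:** on the assignment form, "The patient and researchers unseal it before surgery".
- **Procedure for unblinding {17b}:** "the surgeons including the principal investigator were unblinded to the trial". The section on adherence {11c} adds that "All surgical procedures were performed by the same senior doctor and the same 5-person group".
- **Criteria for discontinuing or modifying allocated interventions {11b}:** the first item is that "Intraoperative examination found that the rotator cuff of the subject was" repairable, in which case direct repair is done. The other two items are withdrawal and loss to follow-up.

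The consent section {26a} treats eligibility as settled in the outpatient department: "Each participant who meets all inclusion criteria and does not meet any exclusion criteria will sign an informed consent form". Study setting {9} likewise has eligibility confirmed before consent and enrolment.

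**The concern.** Randomisation protects the comparison only if nothing that depends on the arm decides who is in it. Here one eligibility criterion is applied after allocation, by the person who knows the allocation, and it turns on what counts as moderate tension. No numeric threshold and no independent reader is given.

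The two operations differ in graft length, fixation and number of anchors, and the protocol says openly that it expects STR to do better. A borderline cuff could be called repairable more often in one arm without any bad faith. Blinded evaluators cannot undo selection that happened in theatre.

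If such patients leave the analysis, the arms may differ in tear severity. If they stay, direct repairs enter a comparison of STR with SCR. The outpatient confirmation of all inclusion criteria also cannot be true of this one.

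**Working it through.** **1. Order of events as written**

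| Step | When | Arm known to surgeon? | Section |
|---|---|---|---|
| Eligibility said to be confirmed, consent, enrolment | Outpatient | No | {9}, {26a} |
| Assignment unsealed | Before surgery | Yes, from here on | {16b}, {17b} |
| Irreparability judged | During surgery | Yes | Inclusion criteria, {11b} |
| Allocated procedure, or direct repair | During surgery | Yes | {11b} |

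Table 1 puts allocation in the treatment-delivery column. That does not place it after the arthroscopic check, and it does not override {16b}.

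**2. The plan's own sample size** (Sample size {14})

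Inputs: ASES 87.6 (SD 5.8) and 93.1 (SD 8.1), two-sided alpha 0.05, power 90%, 15% drop-out, 58 recruited (29 per group). The difference is not stated. It is implied as 93.1 − 87.6 = 5.5.

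Two-sample t test, standardised difference 5.5 / 5.8 = 0.948: n = 24.4, so 25 per group. The stated figure is reproduced. With 15% drop-out, 29 × 0.85 = 24.65 per group remain, with power 0.903.

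**3. Loss of numbers if repairable cuffs are excluded**

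The protocol gives no rate q of cuffs found repairable, so q is an assumption. Evaluable per arm = 29 × (1 − q) × 0.85. Power is from the noncentral t, difference 5.5, SD 5.8.

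| q (assumed) | Evaluable per arm | Power |
|---|---|---|
| 0 | 24.65 | 0.903 |
| 5% | 23.4 | 0.888 |
| 10% | 22.2 | 0.870 |
| 20% | 19.7 | 0.827 |
| 30% | 17.3 | 0.771 |

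**4. Bias under assumed differential exclusion**

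Let the arms exclude fractions q₁ and q₂, and let excluded patients differ from retained ones by g ASES points. The mean of the retained patients moves by q × g in each arm, so the group difference shifts by (q₂ − q₁) × g. None of these inputs is in the protocol.

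- Rates 10% and 10%: shift 0.
- Rates 10% and 20%, g = 2.9 (half an SD): 0.10 × 2.9 = 0.29 points, 5% of 5.5.
- Rates 10% and 30%, g = 5.8 (one SD): 0.20 × 5.8 = 1.16 points, 21% of 5.5.

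The zero in the first line also requires that the same kind of patient is excluded in both arms.

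**The case against.** **Exclusion from the analysis is not stated.** Section {11b} concerns the intervention. It does not say that a patient with a repairable cuff leaves follow-up or the analysis. Rules for analysis sets may stand in an analysis plan that is not shown, and the flow chart is not visible. A reader might infer that these patients are certainly dropped. The text does not support that; it supports only that they may be, since they fail an inclusion criterion and are listed beside withdrawal and loss to follow-up. It is also not certain that the 15% drop-out leaves them out, although {20c} calls that allowance loss to follow-up. This objection stands and limits the claim, but does not remove it: a retained patient would still have received neither study procedure on an arm-aware decision.

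**There are partial safeguards.** The test is a described manoeuvre, the intervention description puts arthroscopic confirmation before the arm-specific steps, and every operation is filmed. These make a call auditable afterwards. They do not hide the arm from the person making it.

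**A larger loss of power is tempting.** With SD 8.1 in one arm (average SD √((5.8² + 8.1²)/2) = 7.04), power would be about 72% or 67% at 10% or 20% exclusions. But under those SDs it is already about 77% with none, so most of the fall from 90% comes from the choice of SD, a separate matter.

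**Block sizes are a side issue.** The "variable block sizes of two, four and eight patients" might seem to make things worse. In a simulation, guessing the lagging arm is right 69% of the time with these blocks and 68% with blocks of four, six and eight. That adds little where the surgeon already knows the arm, and it is not part of this point.

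**Conclusion.** The point holds as a fault in the order of trial steps. Followed as written, the protocol puts a subjective eligibility decision after allocation, in the hands of an unblinded surgeon, and no other section cures it.

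The main harm is possible selection bias. The protocol gives no basis for its size or direction; the shifts of 0.29 to 1.16 points are illustrations. A reader might infer that the trial is biased towards STR. The text does not show that: there is no evidence that calls differ by arm.

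The loss of numbers is modest at the protocol's own SD: from 90% to 87% or 83%, if 10% or 20% are found repairable, if they are excluded, and if this comes on top of the 15% drop-out. The case for change rests on the bias route, which cannot be repaired once patients have been lost this way, and less on the power.

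**What to change.** Keep consent and baseline assessment before surgery. Randomise in the Castor system already in use, or have a member of staff open the sealed assignment, in theatre and only after irreparability has been confirmed arthroscopically and recorded. The operative video can carry the time of that record.

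Amend {16b} so that the patient neither unseals nor receives the assignment. A patient under general anaesthesia could not do so at that moment, and the change also protects the patient blinding that {17a} promises. Align {9} and {26a}: outpatient eligibility is provisional on the intraoperative criterion.

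Cuffs found repairable are then screen failures, never randomised, and are reported as such in the flow chart. The 58 are counted from randomisation. What is done surgically for a repairable cuff is untouched.

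Cost: an amendment with ethics committee approval and notice to participants (section {25}) in a trial that has been recruiting since January 2024; both set-ups kept ready in theatre until the arm is known; and more patients consented. Under the assumed 10% to 20%, 58 / 0.9 = 64.4 and 58 / 0.8 = 72.5, so about 64 to 73 patients must consent to reach 58 randomised.

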### Strategies to improve adherence to interventions {11c}

All surgical procedures were performed by the same senior doctor and the same 5-person group.

### Relevant concomitant care permitted or prohibited during the trial {11d}

#### Postoperative rehabilitation

Post-surgery, the patients were placed in a brace in a neutral position with a small abduction pillow to protect the reconstructed area. Full active range of motion of the elbow, wrist, and hand was allowed immediately. The patient wore the sling at all times, except while showering and during formal physical therapy, for the first 6 weeks. After 6 weeks, the patient was instructed to perform closed-chain passive table slides and scapular stabilization exercises. Active range of motion and strengthening exercises were started approximately 3 months post surgery.

### Provisions for posttrial care {30}

Trial participants will receive a free MRI scan at 12 months postoperatively and treatment for any complications.

### Outcomes {12}

Imaging data, VAS score, active and passive motion of the shoulder joint, and Constant and AESE scores of the shoulder joint were collected before surgery and 3, 6, 12 and 24 months after surgery. The results of the surgical treatment were studied via preoperative and postoperative imaging scans and various data scores (Table 1).

**Table 1 Tab1:** Trial schedule according to the recommendation in the interventional trial (SPIRIT) guidelines

Timepoint	Prerandomization	Treatment delivery	3 months postoperative	6 months postoperative	12 months postoperative	24 months postoperative
**Enrolment:**						
Eligibility screen	×					
Informed consent	×					
Baseline questionnaire	×					
**Allocation**						
SCR		×				
STR		×				
**Assessments**						
ASES	×		×	×	×	×
UCLA	×		×	×	×	×
VAS	×		×	×	×	×
Constant-Murley shoulder score	×		×	×	×	×
Range of motion	×		×	×	×	×
Hamada classification	×		×	×	×	×
Shoulder abduction muscle strength (IMS and EMG)	×			×	×	×
Operation time		×				
Intraoperative blood loss		×				

*IMS*, Isokinetic muscle strength testing

#### Primary outcome

The ASES score and the Constant-Murley shoulder score were obtained during the preoperative stage, as well as at 3 months, 6 months, 12 months and 24 months.

#### Secondary outcome

Postoperatively, the improvement in shoulder function was evaluated. Additionally, the range of motion was recorded for shoulder joint active forwards flexion, abduction, lateral rotation, and internal rotation behind the back, with the latter recorded using vertebral levels ranging from C1 to S5, classified into grades 1–29. During the preoperative stage, as well as at 3 months, 6 months, 12 months and 24 months postoperatively, the VAS was employed to assess the improvement in shoulder joint pain.The Hamada classification was used to assess the degree of arthritis and measure AHD on anterior–posterior X-ray images during the preoperative stage, as well as at 3 months, 6 months, 12 months and 24 months postoperatively. During the preoperative stage, as well as at 3 months, 6 months, 12 months and 24 months postoperatively, Warner classification and Goutallier grading were employed on MRI oblique sagittal images to evaluate supraspinatus muscle atrophy and fatty infiltration. The integrity of the rotator cuff was determined using the Sugaya classification on MRI coronal images.The operation time and intraoperative blood loss were recorded immediately after the operation, and the postoperative drainage volume was recorded after the operation.

#### Other evaluation

Safety indicators: At 6 weeks, 3 months, 6 months, and 12 months following the surgical procedure, the occurrences of adverse events such as infections, fat embolism, deep vein thrombosis in the lower extremities, and retearing were documented.Isokinetic muscle strength testing and surface EMG testing were used to evaluate the improvement in shoulder abduction muscle strength during the preoperative stage, as well as at 6 months, 12 months and 24 months postoperatively.

#### Participant timeline {13}

The participant timeline is shown in Fig. 1.

### Sample size {14}

Sample size calculation for ASES score analysis was performed with an expected standard deviation (SD) of 5.8, a significance level at 5% and power of 0.90 and resulted in 25 participants in each group (50 participants with allowance for 15% drop-out).

In our previous research on postoperative ASES scores of SCR, the score was 87.6 ± 5.8 at the latest follow-up. The best ASES result published by Mihata was 93.1 ± 8.1 (Structural and clinical outcomes after superior capsule reconstruction using an at least 6-mm thick autogenous fascia latas including the intermuscular septum). With a type I error rate of 0.05 (*α* = 0.05, two-tailed) and a power of 90% (*β* = 0.10), the sample size for the study protocol was calculated as 25 patients per group based on the primary outcome indicator by PASS 2021 (Power Analysis and Sample Size, NCSS, LLC, USA). Assuming a 15% drop-out rate, we plan to recruit 58 participants (29 per group) to the study.

### Recruitment {15}

Assuming a 15% drop-out rate, we plan to recruit 58 participants (29 per group) for the study.

## Assignment of interventions: allocation

### Sequence generation {16a}

Randomization will be performed using a computerized randomization procedure in https://castoredc.com. The enrolled patients were randomized in a 1:1 ratio into two treatment groups (the STR group and the SCR group). Patients will be randomized in a 1:1 ratio using variable block sizes of two, four and eight patients, stratified for two treatment groups (the STR group and the SCR group) to avoid imbalances between groups. The order of the block sizes is unknown to the researchers.

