### Trial design {8}

The trial is designed as a 1:1 randomized, controlled, observers and patients double-blinded single-centre trial with two parallel groups, which will compare the STR versus SCR using autogenous fascia latas for the repair of IPMRCT. The enrolled patients were randomized in a 1:1 ratio into two treatment groups (STR group and SCR group) by a simple computer-generated randomization system (https://castoredc.com). Double-blinding was used, in which patients and evaluators were blinded to minimize ascertainment bias. It was registered in the Chinese Clinical Trial Registry (ChiCTR.org ID: ChiCTR2300073716). The study protocol was approved by our institutional review board, and all subjects will be asked to finish a written informed consent. The flow chart of the inclusion and exclusion of trial participants is given in Fig. 1.

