### Interventions

#### Explanation for the choice of comparators {6b}

Mihata proposed SCR with the autogenous fascia latas in 2012 to treat irreparable MRCTs [6]. The SCR can restore the stability of the upper part of the shoulder joint and avoid excessive upwards movement of the humeral head and the impact of the shoulder peak. For irreparable MRCT, SCR can restore the stability of the upper part of the glenohumeral joint and the function of the shoulder joint.

STR involves the fixation of one end of the graft in the footprint and the other end in the medial spine of the scapula, with the aim of achieving muscle-fascial fusion by the 6^th^ postoperative week. Following STR, the SSP may transmit the contraction force to the humerus, thus restoring the anatomy and dynamic function of the rotator cuff. However, whether STR could achieve a better clinical outcome than SCR is still not known.

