### Methods for additional analyses (e.g. subgroup analyses) {20b}

No additional analyses were performed.

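### The stated stratification factor is the treatment arm itself, so no baseline factor is balanced by design, and supraspinatus muscle quality is not adjusted for in the stated comparisons

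*Protocol article*

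**What the plan says.** **Allocation.** Sequence generation {16a} gives the method: "Patients will be randomized in a 1:1 ratio using variable block sizes of two, four and eight patients". The same sentence continues: "stratified for two treatment groups (the STR group and the SCR group) to avoid imbalances between groups". No age band, tear size, baseline score or imaging grade is named as a stratification factor there or elsewhere. Trial design {8} says that patients were randomised "by a simple computer-generated randomization system" and mentions neither blocks nor strata.

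**Muscle quality.** The choice of comparators {6b} explains how STR should work: "Following STR, the SSP may transmit the contraction force to the humerus, thus restoring the anatomy and dynamic function of the rotator cuff". The Discussion gives the same mechanism and contrasts it with the passive stability that SCR provides. The imaging limit on joint condition is "Preoperative imaging examination Hamada classification within type 3", which grades arthritis. Neither list of criteria mentions Goutallier or Warner grade. Both grades are taken before surgery and at each follow-up, as secondary outcomes: "Warner classification and Goutallier grading were employed on MRI oblique sagittal images to evaluate supraspinatus muscle atrophy and fatty infiltration".

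**Analysis.** Statistical methods {20a} compares metric outcomes such as ASES by t test or Mann-Whitney U test, and the ordinal imaging grades by a rank-sum test. It names no covariate. Section {20b} adds: "No additional analyses were performed".

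**The concern.** A stratification factor must be known before a patient is allocated. The arm is not, so the clause describes something that cannot be done. A reader or a later systematic reviewer would take it that some prognostic factor had been balanced by design, and none was.

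The natural candidate is the condition of the supraspinatus muscle. The protocol expects STR to do better because it carries that muscle's force to the humerus, so it is reasonable to expect the result to depend on how much working muscle is left. The grade is already collected before surgery, yet the design and the stated tests make no use of it for balance or precision. With 29 patients per arm, chance can leave the arms visibly different on it, and an unadjusted comparison then carries that difference into the ASES contrast.

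**Working it through.** **1. The plan's own figure.** Sample size {14} gives SCR 87.6 with SD 5.8 and a comparison mean of 93.1, so the difference is 93.1 − 87.6 = 5.5. At two-sided 5% and SD 5.8, the exact t test has power 0.895 with 24 per group and 0.907 with 25, so 25 per group reproduces. Then 25 × 1.15 = 28.75, rounded up to 29 per group and 58 in total. These figures set the arm size below and are not in dispute here.

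**2. What the blocks achieve.** In 20,000 simulated lists of 58 patients in random blocks of 2, 4 and 8, the arm sizes never differed by more than 4, and differed by 4 in about 0.35% of lists. With simple randomisation in the technical sense, a difference of 8 or more would occur with probability 36%. The blocks therefore deliver equal arm sizes, and the stratification clause adds nothing to them.

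**3. Chance imbalance in a baseline factor.** Let K of the 58 patients have advanced fatty infiltration and let X be the number in one arm of 29. Then X is hypergeometric (58, K, 29), and the arms differ by |2X − K|/29. The prevalence is not in the protocol; 30% to 50% is assumed, so K runs from 17 to 29.

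The count difference |2X − K| is odd when K is odd and even when K is even. Fifteen points is 4.35 patients and 20 points is 5.8 patients. For odd K the thresholds are therefore differences of 5 and 7; for even K both thresholds are 6. Odd and even K must both be shown:

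| K (share of 58) | P(≥15 points) | P(≥20 points) |
|---|---|---|
| 17 (29%) | 24.8% | 8.2% |
| 18 (31%) | 15.5% | 15.5% |
| 23 (40%) | 28.3% | 10.6% |
| 24 (41%) | 18.2% | 18.2% |
| 28 (48%) | 18.9% | 18.9% |
| 29 (50%) | 29.4% | 11.4% |

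Over all K from 17 to 29 the ranges are 15.5% to 29.4% and 8.2% to 18.9%. At about 20% prevalence (K = 12) both probabilities are 10.3%.

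**4. What real stratification would do.** With the same blocks run separately in two muscle-grade strata (10,000 simulated trials at each of 20%, 30% and 50% prevalence), a difference of 10 points or more occurred in fewer than 0.5% of trials, and one of 15 points or more in none. Without strata, 10 points or more has probability 33% to 60% at those prevalences.

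**5. What an imbalance would do to the ASES contrast.** The shift is the imbalance times the effect of poor muscle on ASES. That effect is not in the protocol; 5.8 points (one SD) and 10 points are assumed.
- Effect 5.8: 0.15 × 5.8 = 0.87 and 0.20 × 5.8 = 1.16 points.
- Effect 10: 0.15 × 10 = 1.5 and 0.20 × 10 = 2.0 points.

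The standard error at 25 per arm is 5.8 × √(2/25) = 1.64. The shifts are thus about 0.5 to 1.2 standard errors, or 16% to 36% of the planned 5.5.

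**6. What adjustment would gain.** If the factor is binary with prevalence p and an effect of one SD, it explains p(1 − p) of the within-arm variance: 0.3 × 0.7 = 21% to 0.5 × 0.5 = 25%. The standard error is then multiplied by √0.79 = 0.89 to √0.75 = 0.87, so it falls from 1.64 to between 1.46 and 1.42, before any gain from baseline ASES.

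**The case against.** The strongest reply is that this is a slip of wording. The imbalances that the clause means to avoid may be in group size, and the blocks in the same sentence prevent those. The word simple under Trial design may be plain English and not a technical term. Leaving out stratification is legitimate, and picking Goutallier grade over age, tear size or baseline score is a judgement. Shifts of this size are chance variation that the p value already allows for.

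Most of that stands, and it limits the point. It does not rescue the clause, which still claims a stratification that cannot exist. Nor does it rescue the two inconsistent descriptions of the scheme. The Data Availability section says that this article is the full protocol, so the wording cannot be read as a shortened version of a correct one.

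Three stronger readings are tempting, and the protocol supports none of them.
- A reader might infer that the comparison is biased. It is not: randomisation balances muscle quality in expectation, and the unadjusted test is valid.
- A reader might infer that muscle quality is the factor most likely to decide the trial, and that SCR does not need the muscle. The protocol says neither; it says only that SCR does not restore the tendon's dynamic function and gives passive stability.
- A reader might infer that a null result could not be interpreted. The protocol also collects isokinetic strength and surface EMG before surgery and from 6 months, and serial muscle grades, all of which would help to explain one.

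It would also be wrong to say that the grades are absent from the analysis. They are compared between groups as outcomes; what is missing is their use as a baseline covariate.

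**Conclusion.** The point holds in a limited form. The stratification clause is wrong as written, the two descriptions of the randomisation disagree, and a baseline grade tied to the protocol's own mechanism goes unused in the stated comparisons. The consequence is avoidable chance imbalance and lost precision. At 29 per arm and an assumed prevalence of 30% to 50%, the probability of an imbalance of at least 15 points is about 15% to 29%, and of at least 20 points about 8% to 19%. The effect on ASES depends on a further assumption; at 5.8 to 10 points, such imbalances would move the contrast by about 0.9 to 2.0 points. The correction to the wording is needed whatever these assumptions turn out to be. The case for the covariate is that it protects against chance imbalance and gains precision using data already collected.

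**What to change.** 1. In Sequence generation {16a}, delete the clause "stratified for two treatment groups (the STR group and the SCR group) to avoid imbalances between groups". Describe the scheme there and in Trial design {8} in the same words: 1:1 allocation by computer-generated permuted blocks of 2, 4 and 8, unstratified.
2. In Statistical methods {20a}, compare ASES between arms with a linear model (ANCOVA) that adjusts all patients, not a subset, for baseline ASES and preoperative supraspinatus Goutallier grade: ASES after surgery = β₀ + β₁·STR + β₂·baseline ASES + β₃·Goutallier grade. State how the grade is coded before any outcome is seen by arm; the protocol gives no cut-off.
3. Optional: stratify by Goutallier grade, only if recruitment is still open. Trial status gives January 2024 to January 2026 as the recruitment period, and the amendments section {25} requires ethics approval for a change of design.
4. Optional: add to section {20b} an STR–SCR estimate by Goutallier stratum, labelled exploratory. At the assumed prevalence each stratum has roughly 9 to 20 patients per arm, so the intervals will be wide.

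Items 1 and 2 cost a few sentences and use measurements already planned. The sample size stays at 58. Eligibility is unchanged, and no view is taken on whether muscle quality should limit it.
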